**Figure 2 F2:**
[figure not shown]
Schematic demonstrating the integration of AI solutions into the normal clinical workflow (AIDOC Copyright 2024 - Proprietary and Confidential). AI, artificial intelligence; EHR, electronic health record; PACS, picture archiving and communication system; RIS, radiology information system.

##### Comparator cohort: usual care

In the comparator cohort, AI will be applied retrospectively and will not influence clinical decision-making at the time of initial scan reporting. This cohort will represent usual care and inform the accuracy and potential clinical utility of integrated AI technology for acute PE.

##### Intervention cohort: AI technology plus usual care

AI tools will be integrated prospectively into radiology workflows within the intervention cohort. The AI technology features a priority flagging system which alerts radiologists to suspected PE cases. This prioritisation process does not re-order the RIS queue or auto-populate any radiology report. Instead, the AI software generates key-slice images and RV:LV ratio overlays that are directly accessible within the PACS and AIDOC Desktop App. This allows the reporting radiologist to consider the AI output at their discretion when reporting. Verification of the final radiology report will remain the responsibility of the reporting radiologist.

For CTPAs not analysed by the AI technology due to technical issues, standard reporting procedures will be followed.

During the intervention phase, radiologists will have the option to provide direct feedback on AI outputs via the priority flagging system, including free-text commentary if desired. All cases in which there is a discrepancy between the AI output and radiology report will be reviewed by the research team as part of a predefined sub-analysis. This will allow assessment of radiologist engagement with the AI outputs, its diagnostic accuracy and clinical relevance in routine practice.

##### Unequivocal PE

The research team will only intervene if the AI software identifies an unequivocal acute PE that appears to have been missed or not reported in the intervention cohort. These cases will be escalated to a thoracic radiologist for urgent review to ensure appropriate treatment. A study-specific standard operating procedure has been designed to manage this process while maintaining patient safety.

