### Study design

This pragmatic, single-centre, non-randomised, quasi-experimental cohort study will evaluate clinical and radiological outcomes in two distinct patient cohorts. The comparator cohort is defined as *usual care*; general radiologist reporting of CTPA. This cohort will consist of patients recruited retrospectively, prior to implementation of the AI. The intervention cohort is defined as *integrated AI technology AND usual care*; general radiologist reporting of CTPA with access to AI technology for acute PE detection. This cohort will consist of patients recruited prospectively, following the implementation of the AI.

The study will consist of three distinct phases. The pre-implementation and post-implementation phases will derive the comparator and intervention cohorts, respectively. The implementation phase will ensure installation, testing and appropriate training of the AI technology. Figure 1 outlines the study structure.

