### Interventions

#### CT report interpretation

All radiology reports for consecutive CTPAs in the comparator and intervention cohorts will be reviewed by a respiratory registrar with 8 years’ clinical experience. The reports will be classified as either positive or negative for acute PE. In cases of uncertainty, adjudication will be performed by a second senior clinician.

The same registrar and a second clinician, blinded to each other’s decisions, will independently assess the reports for radiologist assessment of RHS. Reports will be categorised as either positive, negative or ‘no comment’ for RHS. Discrepancies will be resolved through discussion and, if required, arbitration from a third clinician. This approach will establish a consistent comparator for evaluating AI outputs.

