##### Clinical management

Royal United Hospitals Bath NHS Foundation Trust does not currently have a dedicated Pulmonary Embolism Response Team or onsite percutaneous thrombectomy service. There are no plans to implement either of these during the study period. Consequently, acute PE management follows standard clinical pathways.

The AI acts as an adjunct to routine clinical care, supporting detection of acute PE and automated assessment of RHS. We therefore anticipate any outcome differences will reflect how radiologists incorporate AI-derived findings into their reports and how clinicians act on them, rather than the influence of specialist services or advanced interventional pathways.

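### A study-run rescue of AI-flagged, unreported PEs exists in the intervention cohort only, so the before/after comparison mixes its effect with that of AI-assisted reporting

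*Protocol article*

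**What the plan says.** Under Study design, the intervention is "general radiologist reporting of CTPA with access to AI technology for acute PE detection", added to usual care. No check by the study team appears in that definition.

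Two later sections add one. Under Intervention cohort: AI technology plus usual care, the article says "All cases in which there is a discrepancy between the AI output and radiology report will be reviewed by the research team as part of" an analysis planned in advance. Under Unequivocal PE it says, of the intervention cohort, "The research team will only intervene if the AI software identifies an unequivocal acute PE that appears to have been missed or not reported in" that cohort. It continues: "These cases will be escalated to a thoracic radiologist for urgent review to ensure appropriate treatment", and "A study-specific standard operating procedure has been designed to manage this process while maintaining patient safety".

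For the comparator cohort, "AI will be applied retrospectively and will not influence clinical decision-making at the time of initial scan reporting". No live rescue is described there.

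The primary outcome (Statistical analysis, Table 1) is the proportion of decisions in line with best-practice guidelines, compared before and after AI. Mortality, bed days, time to anticoagulation, risk class and referral are also before/after comparisons. Under CT report interpretation, "The reports will be classified as either positive or negative for acute PE"; the section does not say which version of a report is read if it was changed after escalation. On attribution, Clinical management says: "We therefore anticipate any outcome differences will reflect how radiologists incorporate AI-derived findings into their reports and how clinicians act on them", as opposed to specialist services or advanced interventional pathways.

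**The concern.** An escalated patient is one whose PE the AI flagged and the AI-assisted radiologist appears not to have reported. The study team then acts, and the patient can enter the results as a diagnosed and treated PE. A comparator patient with the same missed PE had no such route: the AI was run only afterwards, so the patient stays report-negative.

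The two cohorts thus differ in two respects, access to AI and presence of the rescue, while the comparison is read as the effect of the first. The primary outcome is affected, and the likely direction for concordance and treatment favours the product under evaluation. Unless the first report and the time of escalation are kept, the rescue's contribution can be neither measured nor removed later.

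Time zero adds to the problem. Table 1 counts mortality from PE diagnosis. For an escalated patient that date falls after the CTPA, so the interval from scan to escalation drops out of follow-up.

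**Working it through.** The article gives no power calculation and no rescue rate, so there is no planned figure to reproduce. What follows is a check of scale.

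**Inputs from the article (Sample size):** about 3500 CTPAs over 24 months; PE prevalence 12% to 15%.

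**Assumptions (not in the article):** equal split between the two 12-month cohorts; share *s* of intervention-cohort PEs that are rescued, 2% to 8%; baseline concordance *p*, 60% to 80%; every rescued patient ends with a concordant decision.

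**Step 1, PEs per cohort.** 3500 / 2 = 1750 CTPAs. 1750 × 0.12 = 210; 1750 × 0.15 = 262.5.

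**Step 2, rescued patients.** 210 × 0.02 = 4.2; 262.5 × 0.08 = 21. So about 4 to 21.

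**Step 3, shift in concordance.** This depends on where an unrescued miss would have been counted, which the article does not settle.

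- *Outside the PE group*, as a report-negative comparator patient would be. Rescue adds concordant patients to the group: shift = [p(1 − s) + s] − p = s(1 − p). Smallest: 0.02 × 0.20 = 0.4 points. Largest: 0.08 × 0.40 = 3.2 points.
- *Inside the PE group as non-concordant.* Each rescue turns a failure into a success: shift = s, or 2 to 8 points.
- *All CTPAs as denominator.* 4.2 / 1750 = 0.24 points; 21 / 1750 = 1.2 points.

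**Step 4, effect on the test.** With 210 to 262 PE patients per cohort, a two-sided 0.05 test of two proportions, baseline 60% to 80% and no true AI effect, the chance of a significant result in favour of AI (nominally 2.5%) is:

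| Shift from rescue alone | Chance of a significant pro-AI result |
|---|---|
| 1 point | about 4% to 5% |
| 3 points | about 9% to 14% |
| 5 points | about 18% to 33% |

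The difference detectable with 80% power on the same assumptions is about 9 to 13 points. A shift of 0.4 to 3 points is therefore small beside what the study can detect, but it works in one direction for concordance.

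**Step 5, direction for other outcomes.** A rescue follows a missed report, so it may lengthen recorded time to anticoagulation in the intervention cohort. For mortality, rescue may help the patient, but it also moves patients into the PE group whose risk relative to the others is unknown. Neither sign follows from the text.

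**The case against.** Much can be said on the other side.

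- *An article leaves such detail to the full protocol, SOP or SAP.* This is true of which report version is coded, how escalations are logged and which sensitivity analyses are run; silence on these is not the finding. The one-sided rescue and the attribution sentence, however, are both stated in the article.
- *The cases are identifiable.* This stands. Discrepancies are reviewed as a predefined sub-analysis, and all PE-positive and discrepant cases are reviewed under Artificial intelligence accuracy. That makes the remedy cheap. It does not take the rescue out of the before/after comparison.
- *The rescue is itself an effect of AI.* The AI triggers it, but study staff deliver it. If it is meant to count, the definition under Study design should include it.
- *Patient safety requires it.* Agreed; the procedure is not in question.
- *The attribution sentence is about the absence of a response team and a thrombectomy service.* In context that is its main purpose, and it states an expectation. It is incomplete because it leaves out the escalation route; to call it false would overread it.

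A reader might also infer more than the article supports:

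- *That PE detection and discordance rates are inflated.* In Table 1 these rows are AI-accuracy measures, not before/after comparisons. The expert reference standard is set in the retrospective cohort, where no rescue occurs, and nothing says that escalation erases a recorded discrepancy.
- *That hospitals using the AI routinely would lack this check.* The terms research team and study-specific procedure suggest so, but routine deployment is not described. This is an inference.
- *That every scan gets a second read.* The check is triggered by the AI and limited to unequivocal cases.

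**Conclusion.** The concern holds as a matter of design and attribution. A study-run rescue that can change treatment operates in one cohort only, lies outside the defined intervention and is missing from the article's account of where outcome differences will come from. The before/after comparison as written estimates AI-assisted reporting plus rescue.

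The bias probably favours AI for concordance and treatment. For mortality and time to anticoagulation the direction is open, and a general claim that all outcomes are biased towards AI is not supported.

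The size rests on assumptions. The most natural reading, in which unrescued misses fall outside the PE group, gives roughly 0.4 to 3 points. The 2 to 8 point figure applies only if those misses would have counted as non-concordant PE patients, and over all CTPAs the shift is at most about 0.2 to 1.2 points. If few PEs are missed despite AI, the bias is small. The change is worth making because it is cheap and because the data to make it may not be recoverable later.

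**What to change.** Leave the safety procedure unchanged and alter what is recorded and counted:

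1. Record the first verified report and the date and time of each escalation.
2. In the before/after comparison, classify patients in both cohorts by the first verified report and by decisions made before any escalation. Treat AI-flagged, report-negative patients by one rule in both cohorts; the comparator's can be found from the retrospective AI run. Counting only the intervention cohort's escalated patients as failures would create the opposite bias.
3. Use the CTPA date as time zero for mortality and time to anticoagulation in both cohorts. Participant data already collects outcomes up to 12 months from the CT.
4. Report the number escalated. For outcomes that rescue may already have changed, such as mortality, bed days and referral, give a sensitivity analysis with and without escalated patients in the PE group.
5. Amend the sentence under Clinical management to acknowledge the escalation route.

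The cost is one CRF field, a little more analysis and a possibly smaller apparent AI effect. Patient care does not change.

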##### Clinical management

Royal United Hospitals Bath NHS Foundation Trust does not currently have a dedicated Pulmonary Embolism Response Team or onsite percutaneous thrombectomy service. There are no plans to implement either of these during the study period. Consequently, acute PE management follows standard clinical pathways.

The AI acts as an adjunct to routine clinical care, supporting detection of acute PE and automated assessment of RHS. We therefore anticipate any outcome differences will reflect how radiologists incorporate AI-derived findings into their reports and how clinicians act on them, rather than the influence of specialist services or advanced interventional pathways.

## Methods: data collection, management and analysis

### Data collection and management

For each eligible participant, a structured CRF will be completed to capture relevant data. Only the minimum necessary data required to address the study objectives will be collected. Participants will be assigned a unique study identification code to pseudonymise their data. A cross-referencing list linking identifiers to study codes will be stored securely on a password-protected NHS computer database. All research records will be retained for 5 years, after which they will be securely destroyed.^22^

For the comparator cohort, anonymised CTPA images will be transferred for off-site analysis at AIDOC’s core laboratory (Tel-Aviv, Israel). Prior to image transfer, all imaging will be anonymised in accordance with the Royal United Hospitals Bath NHS Foundation Trust’s information governance protocols to ensure data confidentiality.

In the intervention cohort, AI solutions will be embedded within existing PACS workflows. AIDOC and IMBIO servers will be installed locally, facilitating real-time ‘live’ AI analysis of CTPAs. System integration will be conducted in collaboration with radiology information technology and information governance teams.

### Statistical analysis

#### Clinical and radiological outcomes

Our primary outcome will be the proportion of patient decisions made in line with evidence-based best practice guidelines after introducing AI technology within CTPA reporting. Secondary outcomes relate to acute PE detection, RV:LV ratio quantification and clinical and operational endpoints including mortality, length of stay, readmission, follow-up and cost to NHS (table 1).

**Table 1 T1:** Primary, secondary and additional outcomes

Outcome measure	Measure description
Primary outcome measure	
Proportion of patient decisions made in line with evidence-based best practice guidelines after introducing AI technology within CTPA reporting	Comparison before and after AI introduction
Secondary outcome measures	
Rate of acute PE detection with AI technology	True positives and true negatives
Rate of discordant acute PE cases	False positive and false negative rate with acute PE detection
AI failure rate for acute PE detection	Proportion of scans unable to be interpreted by AI despite suitable CTPA acquisition
Rate of RV:LV detection with AI technology	True positive and true negative
Rate of discordant RV:LV detection	False positive and false negative
Failure rate for automated RV:LV ratio	Proportion of scans unable to calculate automated RV:LV ratio despite suitable CTPA acquisition
30-day mortality	Patient mortality (death) at 30-days post-PE diagnosis. Comparison before and after AI introduction
12-month mortality	Patient mortality (death) at 12 months post-PE diagnosis. Comparison before and after AI introduction
Hospital admission and bed days for acute PE	Comparison before and after AI introduction
Time to anticoagulation in PE cases	Comparison before and after AI introduction
Time from CTPA to discharge	Comparison before and after AI introduction
PE risk stratification rates (low, intermediate low, intermediate high and high risk)	Comparison before and after AI introduction
Cost to NHS for acute PE	Comparison before and after AI introduction
End-user (clinician and radiologist) acceptability of AI technology	Quantified metrics from a non-validated questionnaire to evaluate end-use experience of integrated AI radiology reporting
Referral rates to outpatient follow-up (respiratory, thrombosis, haematology)	Comparison before and after AI introduction
Diagnostic rate of chronic thromboembolic pulmonary hypertension	Comparison before and after AI introduction
Additional outcome measures	
Exploratory outcomes	Given the exploratory nature of this observational non-randomised feasibility study, there may be patterns/outcomes which emerge/develop during the study period. The investigators will report on any patterns that may emerge following the introduction of AI reporting

AI, artificial intelligence; CTPA, CT pulmonary angiography; PE, pulmonary embolism; RV:LV, right ventricular to left ventricular ratio.

Descriptive statistics will summarise participant baseline characteristics and comorbidities, separately in the comparator and intervention cohorts. Our primary analyses will consist of comparisons between the comparator and intervention cohorts, with continuous outcomes analysed using t-tests and categorical outcomes using χ^2^ tests. To account for and disentangle any possible underlying time trends from the effects of AI introduction, regression models will be used to compare outcomes. These will include covariates that allow for a linear trend in the pre-implementation phase, a step change at the point of AI implementation, and a modification to the linear trend following this.

Kaplan-Meier survival curves will quantify differences between time-to-event outcomes in the two cohorts. Cox regression models will also be used to summarise the difference between cohorts. If feasible, regression models will be adjusted for known predictors of outcome from both Geneva and sPESI scoring systems.^20 21^ Missing values will be handled by performing each analysis excluding patients who have relevant data missing for the variables concerned. Statistical significance will be set according to p value <0.05.

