#### Exclusion criteria

Participants will not be eligible for inclusion in the study if any of the following are true:

Aged under 18 years old.Registered with the national opt-out scheme for research.CTPA performed for reasons other than the assessment of acute PE.CTPA reported by external radiologist.CTPA scan which is incomplete or discontinued.

Patients whose CTPA was reported by an external radiologist will be excluded due to difficulty confirming the reporting radiologist’s access to existing AI software. Patients will also be excluded if the clinical indication for CTPA is unrelated to acute PE. The AI software is solely licenced for the assessment of acute PE. No substantial amendments have been made to the eligibility criteria since study inception.

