### Sample size

As a pragmatic real-world quasi-experimental assessment of AI integration, formal power calculations were not feasible. Based on historic imaging volumes, it is anticipated that approximately 3500 eligible CTPAs will be identified across the 24-month recruitment period and that the prevalence of acute PE will be between 12% and 15%.

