#### Artificial intelligence accuracy

We will evaluate AI performance against both the original radiology reports and expert thoracic radiologist reviews, which will serve as the clinical reference standard. Agreement between modalities will be assessed using Cohen’s kappa and measures of diagnostic test performance.

The research team will also review all PE-positive and discrepant cases to evaluate the potential for the AI software to act as a clinical safety net for the detection of acute PE.

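### Both AI failure rates cover only suitable acquisitions, and the detection outcomes have no cell for scans without AI output, so detection across all eligible PEs cannot be recovered

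*Protocol article*

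**What the plan says.** Under Exclusion criteria, the only criterion about the scan itself is "CTPA scan which is incomplete or discontinued". Completed scans of limited quality are not excluded.

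Table 1 (Clinical and radiological outcomes) gives the PE failure rate as "Proportion of scans unable to be interpreted by AI despite suitable CTPA acquisition" and the RV:LV failure rate as "Proportion of scans unable to calculate automated RV:LV ratio despite suitable CTPA acquisition". The article does not define suitable acquisition or say who judges it, or when.

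In the same table, PE detection is described by true positives and true negatives, and discordance by "False positive and false negative rate with acute PE detection". The RV:LV outcomes follow the same pattern. None has a category for no output.

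The missing-data rule in that section reads: "Missing values will be handled by performing each analysis excluding patients who have relevant data missing for the variables concerned". The Artificial intelligence accuracy section adds "Agreement between modalities will be assessed using Cohen’s kappa and measures of diagnostic test performance" and gives no separate rule for scans without output.

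Such scans are foreseen. For the intervention cohort the article says "For CTPAs not analysed by the AI technology due to technical issues, standard reporting procedures will be followed". That settles how they are reported clinically, not how they are analysed.

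**The concern.** The population that enters the study and the population over which AI failure is counted are defined differently. Eligibility depends on the scan having been completed, and the failure rates depend on the acquisition also having been suitable. A scan that meets the first condition but not the second, and has no AI output, has no place in Table 1's AI outcomes.

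This matters because the study sets out to measure real-world performance and to judge whether the AI can act as a safety net. From that standpoint, a PE on which the AI returned nothing is a PE it did not flag. Sensitivity among processed scans answers how good the algorithm is when it runs. The stated aim also needs to know how many of the eligible PEs it finds. Comparator-cohort evidence feeds the decision tree in the health economic model, so a detection figure limited to processed scans could carry over into that model.

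**Working it through.** The article gives no failure rate, so there is no figure of its own to reproduce. The check has two parts: where each type of scan is counted, and simple arithmetic on assumed rates.

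**Where each eligible scan is counted**

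| Eligible scan | Detection cells (TP, TN, FP, FN) | Failure rate |
|---|---|---|
| AI output, suitable acquisition | counted | in denominator |
| No output, suitable acquisition | not counted | counted as failure |
| No output, acquisition called unsuitable | not counted | not counted |

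The third row is the gap. The second row is disclosed, but the failure rate is not split by PE status, so a reader can combine it with sensitivity only by assuming that failure is unrelated to PE.

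**Inputs**
- Scans: "approximately 3500 eligible CTPAs will be identified across the 24-month recruitment period" (Sample size), with PE prevalence of 12% to 15% from the same section.
- Reference-standard subset: 4 months of consecutive comparator scans (Reference standard).
- Sensitivity among processed scans, Se: 97%, the upper figure cited in the introduction, used only as an illustration.
- Share of PE scans with no output, f: 2%, 5% and 10%. These are assumptions.

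**Size of the subset, assuming even accrual**
- 3500 / 24 × 4 = about 583 scans.
- PEs: 583 × 0.12 = 70, and 583 × 0.15 = about 88.

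**Sensitivity over all eligible PEs** = Se × (1 − f)

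| f | PE scans lost from the subset | Sensitivity over all PEs | Gap from 97% |
|---|---|---|---|
| 2% | 1.4 to 1.8 | 0.97 × 0.98 = 95.1% | 1.9 points |
| 5% | 3.5 to 4.4 | 0.97 × 0.95 = 92.2% | 4.9 points |
| 10% | 7.0 to 8.8 | 0.97 × 0.90 = 87.3% | 9.7 points |

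Because 1 − f cannot exceed 1, the direction is fixed: the all-PE figure is never above the processed-only figure.

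**Comparison with sampling error.** The approximate 95% half-width for a sensitivity of 97% is 1.96 × √(0.97 × 0.03 / n). This is 4.0 points at n = 70 and 3.6 points at n = 87.5. The gap is 0.97 × f, so it passes the half-width at f of about 4% (0.036 / 0.97 = 3.7%; 0.040 / 0.97 = 4.1%). Below that level it is smaller than the sampling error.

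**Effect on the reported failure rate.** Let F be the no-output share of all eligible scans and u the share of those called unsuitable. If they leave both numerator and denominator, the reported rate is F(1 − u) / (1 − Fu).
- F = 5%, u = 50%: 0.025 / 0.975 = 2.6%.
- F = 10%, u = 50%: 0.05 / 0.95 = 5.3%.
- u = 100%: 0% for any F.

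The values of F and u are also assumptions.

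**The case against.** The strongest reply is that failure is not hidden. Table 1 prespecifies two failure-rate outcomes, and accuracy among interpreted scans beside a failure rate is a legitimate pair that separates a weak algorithm from a poor scan. Counting no output as not detected is one convention among several. This stands, and is why the processed-only figure should stay. It does not cover failures on acquisitions called unsuitable, which neither half of the pair includes.

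A second reply is that the exclusion rule does not name AI failures and follows the cohort comparisons and survival models, while AI accuracy has its own section. This partly stands: the rule reaches AI accuracy by inference. The inference is reasonable, because the rule applies to each analysis, Table 1's AI outcomes sit in the same section, and no other rule is given. Even without it, the four detection cells have no place for a scan without output.

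A third reply is that the research team will review all PE-positive and discrepant cases for the safety-net question. A reported PE with no AI output would probably be seen in that review. However, the article states no scoring of no output there, and the review does not change Table 1's denominators.

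A fourth reply is that the before-and-after comparisons already reflect real-world impact. That is correct: nothing removes unanalysed scans from the intervention cohort, so the primary outcome is not affected by this point.

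A reader might also infer that suitability is judged once the AI has failed, so that failures can be relabelled to improve the rate. The article does not support this. It is silent on when suitability is assessed and by whom, so it neither shows such a practice nor rules it out.

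**Conclusion.** The point holds for the secondary AI outcomes. As the outcomes are defined, an eligible scan with no AI output is left out of sensitivity, and if its acquisition is called unsuitable it is left out of the failure rate too. Detection among all eligible PEs cannot be recovered from those figures, and it is below the reported sensitivity whenever any PE scan lacks output.

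The direction is certain under that condition, but the size is not known. The illustrative 95.1%, 92.2% and 87.3% rest on a borrowed 97% and on assumed no-output shares of 2%, 5% and 10%. A reader might conclude that the AI's sensitivity will be materially overstated. The article does not support that, because it gives no failure rate and the gap could be negligible. Nor does the point extend to specificity, which need not be overstated among processed scans.

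This is an inexpensive improvement that serves the study's own real-world and safety-net aims.

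**What to change.** - In Table 1, define both failure rates as scans without an AI output over all eligible scans, split by cause (acquisition, technical or transfer, algorithm). Keep the suitable-acquisition rate as a subset, with suitability defined and judged without knowledge of the AI output.
- For accuracy against the expert reads, report sensitivity with every expert-positive scan in the denominator and no output counted as not detected, beside the processed-scans-only figure. Show no-output counts for RV:LV in the same way.
- State that the missing-data exclusion does not apply to absent AI output in that all-scans analysis.

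The cost is a change of wording, a blinded suitability judgement and one extra tabulation from data already held. No planned analysis is removed. The drawback is that the headline failure rate and sensitivity may look somewhat less favourable.
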